### Primary outcome

2.11

The response rate based on 17-item Hamilton Depression Rating Scale (HDRS17) score at week 6 is considered primary outcomes. Response rate is defined as the percentage resulting from the dividing of the scores at baseline from the difference between those of baseline and week 6. The response rate reaches or over 50%, the patient will be defined as a responder; otherwise, the other patients will be considered non-responders. The formula for calculating the response rate is as follows:

$$\text{Response Rate}=\frac{\left(\text{HDRS}17\;\text{score}\;\mathrm{at}\;8\mathrm{th}\;\text{week}-\text{HDRS}17\;\text{score}\;\mathrm{at}\;\text{baseline}\right)}{\text{HDRS}17\;\text{score}\;\mathrm{at}\;\text{baseline}}\times 100\%$$

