#### Inclusion criteria

2.2.1

Patients who provide written consent will be included in the study if they meet the following criteria: (1) age 20–49; (2) meet the Diagnostic and Statistical Manual of Mental Disorders (DSM-IV) criteria for postpartum depression, diagnosed as PPD by a psychiatrist; (3) score of EPDS >12 points, score of HDRS17 > 7, ≤24; (4) volunteer to participate in this study, and can complete the scale evaluation; (5) the onset occurs within 12 months after childbirth.

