### Assessment

2.8

Assessments take place before the onset of the intervention period (T0), 1 week (T1), 2 weeks (T2), 4 weeks (T3) after the intervention has started, and at the end of the intervention (6 weeks after start of the intervention; T4). Follow-up will take place at 12 weeks after the end of the intervention (T5) (Table 1). Each assessment consists of an online questionnaire and a telephone interview. Except HDRS17, the EPDS, WHOQOL and SMCDS are self-report scales, which will be filled out online at T1-T5. The access of online questionnaires will be sent to subjects by researchers in charge of assessment, at the assessment nodes after inclusion. HDRS17 will be assessed by researchers through telephone interview with subjects.

**Table 1 tab1:** Overview of assessment points and measurements used.

	Online screening	Face-to-face interview	T0	T1	T2	T3	T4	T5
			-7 ~ 0d	1w ± 3d	2w ± 3d	4w ± 3d	6w ± 3d	12w ± 3d
In−/exclusion criteria	×							
Witten consent form		×						
Sociodemographic information		×						
Regular health education			×	×	×	×	×	
Internet-based peer education			×	×	×	×	×	
Edinburgh Postpartum Depression Scale			×	×	×	×	×	×
17-item Hamilton Depression Rating Scale			×	×	×	×	×	×
World Health Organization Quality of Life Scale Brief			×	×	×	×	×	×
Self-Efficacy to Manage Chronic Disease Scale			×	×	×	×	×	×
Medical history, medication, therapies		×	×	×	×	×	×	×
Adverse event		×	×	×	×	×	×	×
Assessment of adherence		×	×	×	×	×	×	×
Completion assessment		×	×	×	×	×	×	×
Review by investigator		×	×	×	×	×	×	×

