### Secondary outcome

2.12

(1) Edinburgh Postpartum Depression Scale (EPDS) (25). It is considered the most frequently validated instrument to screen for perinatal depression. The scale consists of 10 items, mainly concerning the factors like depression, anxiety, anhedonia and self-harm/suicide. Higher scores indicate more severe symptoms of postpartum depression.(2) World Health Organization Quality of Life Scale Brief (WHOQOL-BREF) (28). This standardized tool conceptualizes quality of life as personal perception. Physical health, psychological health, social interactions, and environment are the four dimensions that make up WHOQOL-BREF. There are three to eight items in per domain. Additionally, two generic questions on health satisfaction and overall quality of life (Q1 and Q2) are provided. With the exception of 3 items—pain and discomfort, the need for treatment, and negative feelings—each item is based on self-report and scored on a scale of one to five, with higher scores indicating higher quality of life.(3) Self-Efficacy to Manage Chronic Disease Scale (SEMCD) (29). This patient reported scale mainly evaluate symptoms of chronic conditions, functioning, and self-management. This self-efficacy scale for chronic disease patients was developed by Stanford University in the United States. The scale contains 6 items, each item ranging from 1 to 10, with 1 indicating no confidence at all and 10 indicating great confidence. The average score of the 6 items reflected the average level of self-efficacy of patients. A score of 1–3 indicates a low level of self-efficacy, a score of 4–7 indicates a medium level of self-efficacy, and a score of 8–10 indicates a high level of self-efficacy. Its Cronbach’sα coefficient is 0.91, with high reliability and wide application.

Scales information will be collected and managed by corresponding researchers, who are unaware of the group division. To exclude confounding factors, each subject will be evaluated by the same researcher in the duration of trial.

Evaluation time points: all scales will be evaluated at baseline, 1, 2, 4, 6, and 12 weeks after the initiation of intervention.

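### The printed primary-outcome formula contradicts its own prose and the visit schedule: it needs an uncollected week-8 score, and its sign makes every improvement negative

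*Protocol article*

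**What the plan says.** The protocol article defines the primary outcome in section 2.11, in two ways.

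- **Prose.** The time point is week 6: "The response rate based on 17-item Hamilton Depression Rating Scale (HDRS17) score at week 6 is considered primary outcomes". The per-patient quantity is "the percentage resulting from the dividing of the scores at baseline from the difference between those of baseline and week 6". The classification rule is "The response rate reaches or over 50%, the patient will be defined as a responder".
- **Formula.** Directly below, the numerator is the HDRS17 score at the eighth week minus the HDRS17 score at baseline, the denominator is the baseline score, and the result is multiplied by 100%.

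Four other places bear on this:

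- Section 2.12 states that "all scales will be evaluated at baseline, 1, 2, 4, 6, and 12 weeks after the initiation of intervention". Table 1 in section 2.8 gives the same visits with windows of plus or minus 3 days.
- The text of section 2.8 places the last visit differently: "Follow-up will take place at 12 weeks after the end of the intervention (T5").
- Section 2.9 bases the sample size on response when the six weeks of intervention end, with 28.3% responders under health education and 70% under the combined intervention.
- The Methods paragraph of the Abstract gives the primary outcome at weeks 6 and 12.

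**The concern.** The formula and the prose above it disagree on the time point, and the formula and the responder rule disagree on the sign. HDRS17 falls as a patient improves. A quantity computed as later score minus baseline is therefore negative for every improved patient, while the rule asks for a value of at least +50%.

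The response rate is the only endpoint on which the trial is powered. An analyst who works from the formula cannot compute it. One who corrects the week but keeps the sign would count as responders only those patients whose score rises by at least half of baseline.

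The same term also carries two meanings. In section 2.11 response rate is a percentage change within one patient. In section 2.9 it is the proportion of patients who respond.

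**Working it through.** The article gives no worked example of the formula, so there is no figure to reproduce. The sample size in section 2.9 does not enter the argument, except for the illustration in step 4.

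**1. Is there a week-8 score?** Week 8 is day 8 x 7 = 56.

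| Visit | Nominal day | Window (±3 days) |
|---|---|---|
| T4, week 6 | 42 | 39 to 45 |
| T5, week 12 (Table 1) | 84 | 81 to 87 |
| T5, 12 weeks after a 6-week intervention (text of 2.8) | 126 | 123 to 129 |

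Day 56 falls 56 - 45 = 11 days after the week-6 window closes and 81 - 56 = 25 days before the week-12 window opens. The conflicting date for T5 does not help either. No scheduled visit supplies the score.

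**2. What does the sign do?** Substitute week 6 for week 8, and let B be the baseline score and W the later score.

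- As printed: 100 x (W - B) / B
- Subtraction reversed: 100 x (B - W) / B

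| B to W | As printed | Reversed |
|---|---|---|
| 20 to 8 | (8 - 20)/20 = -60%, non-responder | +60%, responder |
| 16 to 8 | (8 - 16)/16 = -50%, non-responder | +50%, responder |
| 12 to 18 | (18 - 12)/12 = +50%, responder | -50%, non-responder |
| 20 to 30 | (30 - 20)/20 = +50%, responder | -50%, non-responder |

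**3. Does this hold for every eligible patient?** The inclusion criterion "score of HDRS17 > 7, ≤24" allows whole-number baselines from 8 to 24. A baseline of B has B lower scores (0 to B - 1), so the number of improving pairs is 8 + 9 + ... + 24 = 17 x 16 = 272.

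- As printed, all 272 values are negative. The one closest to zero is 24 to 23, at -1/24 = -4.2%. None reaches +50%.
- Reversed, a pair qualifies when W is at most B/2, which gives 149 of the 272.

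These are counts of possible score pairs, not of expected patients.

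**4. What would that mean at the planned rates?** With the 38 per group that section 2.9 gives before dropout, the assumed rates imply 38 x 0.283 = 10.8 true responders in the control group and 38 x 0.70 = 26.6 in the intervention group. The printed formula would class all of these, about 37 patients, as non-responders.

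**5. Does the prose settle the matter?** It settles the time point (week 6) and the denominator (baseline). On direction it says only "the difference between those of baseline and week 6". Baseline is named first, but no order of subtraction is stated. The formula is the only place that fixes a direction, and that direction conflicts with the responder rule.

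**The case against.** The strongest reply is that this is a slip that the same section resolves. The prose names week 6, section 2.9 agrees, and rates of 28.3% and 70% make sense only if response means improvement. This stands: the intended endpoint is recoverable, and the fault is a formula that contradicts its prose rather than an endpoint left undefined.

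It may also be said that the formula was meant as an unsigned size of change. The text does not say so, and that reading would not work either: 12 to 18 is a change of 50% in size and would also count as response.

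Two stronger readings are tempting, and the document supports neither.

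- A reader might infer that literal use would reverse the trial's conclusion. That would need enough patients, mostly in the control group, whose HDRS17 rises by half or more. The article gives no figure for this. If such worsening is uncommon, the likelier result is few so-called responders in either group and an uninformative comparison.
- A reader might take the formula as the specification from which the analysis will be programmed. Section 2.10 says that the research group will draw up a statistical plan before the analysis, and that plan is not shown. The formula is a published definition that could be carried into it, no more.

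**Conclusion.** The point holds as a contradiction within the definition of the primary outcome. The equation is fully legible in the text supplied, so this is not a gap left by extraction or by condensing the protocol into an article. As printed, the formula calls for a score that no visit collects. With week 6 substituted, it classes every improved patient as a non-responder (0 of 272 improving score pairs qualify, against 149 with the subtraction reversed) and counts only rises of at least half of baseline as response.

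Followed as written, it could nullify or invert the primary comparison; which of these would occur cannot be told from the document. The counts assume whole-number scores and baselines of 8 to 24. The sign argument needs neither assumption, only that a lower HDRS17 is better. Because the error sits in the only powered endpoint and the correction is certain, it should be made before the analysis.

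**What to change.** 1. In section 2.11, replace the formula with: percentage reduction = (HDRS17 at baseline - HDRS17 at week 6) / HDRS17 at baseline x 100%. Define a responder as a patient with a reduction of 50% or more.
2. Call the per-patient quantity percentage reduction, and keep response rate for the proportion of responders, as section 2.9 uses it.
3. Align the Abstract, which gives the primary outcome at weeks 6 and 12, with the single week-6 time point in sections 2.9 and 2.11.
4. Use the same wording in the statistical plan announced in section 2.10.

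The cost is one formula, two terms and one line of the Abstract. No visit, measurement or sample size changes.

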### Secondary outcome

2.12

(1) Edinburgh Postpartum Depression Scale (EPDS) (25). It is considered the most frequently validated instrument to screen for perinatal depression. The scale consists of 10 items, mainly concerning the factors like depression, anxiety, anhedonia and self-harm/suicide. Higher scores indicate more severe symptoms of postpartum depression.(2) World Health Organization Quality of Life Scale Brief (WHOQOL-BREF) (28). This standardized tool conceptualizes quality of life as personal perception. Physical health, psychological health, social interactions, and environment are the four dimensions that make up WHOQOL-BREF. There are three to eight items in per domain. Additionally, two generic questions on health satisfaction and overall quality of life (Q1 and Q2) are provided. With the exception of 3 items—pain and discomfort, the need for treatment, and negative feelings—each item is based on self-report and scored on a scale of one to five, with higher scores indicating higher quality of life.(3) Self-Efficacy to Manage Chronic Disease Scale (SEMCD) (29). This patient reported scale mainly evaluate symptoms of chronic conditions, functioning, and self-management. This self-efficacy scale for chronic disease patients was developed by Stanford University in the United States. The scale contains 6 items, each item ranging from 1 to 10, with 1 indicating no confidence at all and 10 indicating great confidence. The average score of the 6 items reflected the average level of self-efficacy of patients. A score of 1–3 indicates a low level of self-efficacy, a score of 4–7 indicates a medium level of self-efficacy, and a score of 8–10 indicates a high level of self-efficacy. Its Cronbach’sα coefficient is 0.91, with high reliability and wide application.

Scales information will be collected and managed by corresponding researchers, who are unaware of the group division. To exclude confounding factors, each subject will be evaluated by the same researcher in the duration of trial.

Evaluation time points: all scales will be evaluated at baseline, 1, 2, 4, 6, and 12 weeks after the initiation of intervention.

### Safety

2.13

The steering group members and the assessment researchers will closely observe the psychological conditions of the peer educators and the participants during the whole course of trial. If an adverse event (AE) happened during intervention, it would be assessed and recorded in the case report form (CRF). The relevant adverse events may include deterioration of the depression, aggravating hopelessness, anxiety and somatic symptoms (et al., dizzy, pain). Serious adverse events include self-harm tendency, suicide attempt, and injury-infant behavior. Once a serious adverse event occurs, the participant will be immediately terminated from this trial and will be referred to a psychiatric clinic as soon as possible.

In addition to routine exclusion and monitoring criteria for suicidality, specific measures for symptom emergence during non-usual clinic hours are established. Participants will be provided with a 24/7 emergency hotline connected to on-call psychiatric professionals. Upon reporting suicidal symptoms, the on-call team will conduct immediate risk assessment via phone, dispatch emergency services if necessary, and coordinate with the participant’s primary caregiver for in-person supervision until professional intervention is available. Documentation of all interactions and follow-up actions will be maintained in the participant’s record.

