The secondary objective is to examine health related quality of life, the self-management ability and safety. We hypothesize, that the IPE group will lead to a significantly greater quality of life, better self-management and less adverse event than RHE group.

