##### Procedures

2.6.1.2

(1) Steering group establishment: A multidisciplinary team is formed to oversee intervention design, peer educator training, and quality assurance.(2) Peer educator selection and training: Eligible PPD patients are recruited, trained over 2 weeks, and assessed for competence before participation.(3) Group formation: Enrolled subjects are assigned to WeChat education groups (maximum 11 subjects per group) containing steering group members, peer educators, and participants.(4) Intervention implementation: Under the leadership of the guidance team, peer educators are trained and supervised to implement interventions for the subjects. The intervention measures include:i. The guidance team disseminates curated postpartum dietary, exercise, and psychological adjustment content every Monday, Wednesday, and Friday, with a monthly communication plan;ii. Peer educators provide weekly updates on member dynamics and needs every Friday, with the guidance team responding and adjusting within two working days;iii. A 60–90 min group video chat is organized every Sunday evening, following an interactive process of “sharing—Q&A—summary”;vi. Peer educators focus on experience sharing, presenting emotional management case studies every Tuesday and Thursday, and conducting monthly thematic sessions (e.g., “Postpartum Sleep and Emotional Regulation”), fostering a supportive atmosphere through positive reinforcement to encourage subject participation and mutual assistance.(5) Safety protocol: Intervention is terminated immediately if participants exhibit suicidal tendencies or harmful behaviors, with referral to psychiatric care.

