#### Alternative therapeutic approaches

2.6.6

During the study period, participants are not prohibited from receiving treatments other than the specified intervention. In cases of aggravated symptoms requiring antidepressant therapy, participants will be referred to psychiatric hospitals, where antidepressants will be prescribed by specialist psychiatrists. All details of antidepressant use or other treatments (including type, dosage, administration frequency, duration, and initiation reasons) will be documented in the CRF. These data will be incorporated into the statistical analysis to account for potential confounding from concurrent treatments.

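### Section 2.13 removes a participant from the trial, not just from the intervention, after a serious adverse event, so her scheduled HDRS17 and adverse-event assessments end as written

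*Protocol article*

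**What the plan says.** Section 2.13 (Safety) defines the trigger: "Serious adverse events include self-harm tendency, suicide attempt, and injury-infant behavior". It then gives the consequence, without distinguishing the arms: "Once a serious adverse event occurs, the participant will be immediately terminated from this trial and will be referred to a psychiatric clinic".

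Ordinary worsening is handled differently. The same section lists it among events to be recorded: "The relevant adverse events may include deterioration of the depression, aggravating hopelessness, anxiety and somatic symptoms". Section 2.6.6 adds that "In cases of aggravated symptoms requiring antidepressant therapy, participants will be referred to psychiatric hospitals". Other treatment is allowed there, and the patient is not required to leave.

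For IPE patients, item (5) of section 2.6.1.2 (Procedures) gives a second rule for similar events: "Intervention is terminated immediately if participants exhibit suicidal tendencies or harmful behaviors", again with psychiatric referral. Here it is the intervention that stops, not trial participation.

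These provisions determine what is lost:
- Section 2.11 sets the time of the primary endpoint, the HDRS17 response: "score at week 6 is considered primary outcomes".
- Section 2.8 and its Table 1 schedule HDRS17, the other scales and adverse-event recording through T5.
- Section 2.8 also states the mode of assessment: "HDRS17 will be assessed by researchers through telephone interview with subjects". The other scales are completed online.
- Section 2.10 assigns missing data to multiple imputation.
- The end of the Introduction gives, as part of the secondary hypothesis, "better self-management and less adverse event than RHE group".

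**The concern.** Stopping study treatment and stopping data collection are separate decisions, and section 2.13 as worded makes both at once. The patients concerned are those whose course has just turned seriously worse, so the missing values depend on the outcome.

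Three things are at stake:
- **Primary outcome.** If the event precedes week 6, response status is imputed. Under missing-at-random, the imputed value borrows from patients who stayed and had no such event, and may be too optimistic.
- **Later and repeated data.** HDRS17 and the other scales up to T5 are lost to the longitudinal GEE model of section 2.10.
- **Safety.** The triggering event is recorded, but scheduled recording of further events then stops for the patients at highest risk, in a trial that hypothesises fewer adverse events with IPE.

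The two rules also conflict. An IPE patient with a tendency to self-harm falls under both 2.6.1.2 and 2.13, with different consequences for her data.

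**Working it through.** **Reading the provisions side by side**

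| Situation | Section | Stated consequence | Leaves the trial? |
|---|---|---|---|
| Worsening depression, hopelessness, anxiety | 2.13 | Recorded as an adverse event | No |
| Worsening that needs antidepressants | 2.6.6 | Referral; treatment documented | Not stated |
| Suicidal tendency or harmful behaviour, IPE | 2.6.1.2 (5) | Intervention stopped; referral | Not stated |
| Serious adverse event, either arm | 2.13 | Terminated from the trial; referral | Yes |

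Only the last row removes the patient. The hotline paragraph of 2.13 promises that contacts and follow-up actions will be kept in the patient's record. That is clinical documentation, not a scheduled HDRS17 or adverse-event assessment. No other section provides for assessment after this exit.

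**Illustration of size**

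The article gives no figure for this point, so there is none to reproduce. The inputs from section 2.9 are 44 randomised per arm and planned response rates of 70% (IPE) and 28.3% (RHE), a difference of 70 - 28.3 = 41.7 points.

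Assumptions, which are mine and not the protocol's: the planned rates hold for all 44 per arm; *k* patients leave before week 6 and are truly non-responders; they are imputed at the response rate of the 44 - *k* who remain, ignoring their own earlier scores.

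- Expected responders: IPE 0.70 × 44 = 30.8; RHE 0.283 × 44 = 12.452.
- Apparent rate after imputation: responders / (44 - *k*).

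| *k* | IPE apparent rate | RHE apparent rate |
|---|---|---|
| 1 | 30.8/43 = 71.6% (+1.63) | 12.452/43 = 29.0% (+0.66) |
| 4 | 30.8/40 = 77.0% (+7.00) | 12.452/40 = 31.1% (+2.83) |

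Shift in the planned 41.7-point difference (IPE minus RHE):

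| Where the losses fall | *k* = 1 | *k* = 4 |
|---|---|---|
| IPE only | +1.6 | +7.0 |
| RHE only | -0.7 | -2.8 |
| *k* in each arm | 1.63 - 0.66 = +1.0 | 7.00 - 2.83 = +4.2 |

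Four patients are 4/44 = 9.1% of an arm. These counts are assumed and are not a bound. An imputation model that uses the patients' T0 to T3 scores would shrink the shifts.

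Power is not the issue. At the planned rates it is 98.4% with 44 per arm and still 95.9% with 36.

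**The case against.** The strongest reply is that 2.13 is one loosely worded sentence in a condensed article. Since 2.6.1.2 pairs the same referral with stopping only the intervention, both may be meant as a single rule, and neither says outright that data collection ends. That is possible. But the wording differs where it matters, nothing in the text says that assessments continue, and staff following 2.13 literally would stop them. If only the intervention was meant, the remedy is the same sentence.

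A second reply is that events will be rare, and that the largest shift needs four of them before week 6, all in IPE, all non-responders, with earlier scores ignored. This stands. Section 2.2.2 excludes a suicidality item score above 2 and suicidal behaviour in the past year, and no direction of bias is established. The count need not be zero, however: item scores up to 2 are eligible, and a tendency to self-harm is a wider criterion than an attempt.

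Third, how to count a missing week-6 outcome may belong in the statistical plan that section 2.10 promises. This also has force. Such a rule would largely protect the binary week-6 endpoint, but it would not recover later HDRS17 scores, the other scales, T5 or further adverse events. The wording of 2.13 therefore remains at issue wherever the analysis rule is placed.

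Finally, the change affects conduct under an ethics-approved protocol and may need an amendment. Recruitment was to reach its target before March 2025, so the rewording may reach few patients. This limits the benefit but does not make the present rule sound.

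**Conclusion.** The concern holds. As written, section 2.13 ends scheduled efficacy and safety assessment for patients who have a serious adverse event, and it disagrees with 2.6.1.2 on overlapping triggers. The resulting missing data are related to outcome and avoidable.

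The size is unknown and probably small. Under the assumed counts, the shift in the planned difference runs from -2.8 points (four lost in RHE only) to +7.0 points (four lost in IPE only). The sign depends on which arm loses patients, and use of earlier scores would reduce the shift. The conclusion rests on the literal wording and on the absence of any other provision for follow-up, not on these figures. The change is worth making because it costs little, not because the primary result is shown to be at serious risk.

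**What to change.** Reword section 2.13 so that a serious adverse event stops the study intervention and triggers immediate psychiatric referral. The telephone HDRS17, online scales and adverse-event assessments should continue to T5 for participants who still consent and for whom this is clinically safe. Make 2.6.1.2 and 2.13 state the same rule.

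Specify, in the protocol or the statistical plan, that a week-6 outcome still missing after such an event counts as non-response, at least as a sensitivity analysis. This can still be fixed after enrolment closes if the data have not been analysed.

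The cost is one sentence of protocol wording, one analysis rule and a few telephone calls within the existing schedule, plus ethics approval of the wording if required. No new staff or procedures are needed.
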